#### 2.2.2. Recruitment of Participants

Participants will be recruited from the four hospitals mentioned above in outpatient clinics. Posters will be used outside the acupuncture clinics. The posters will contain brief introductions about the inclusion/exclusion criteria, the free acupuncture treatments offered to eligible participants, and the contact information of the researchers.

#### 2.2.3. Inclusion Criteria

Participants who meet all the following requirements will be allowed for enrollment:nulliparous women, aged between 18 and 30 years old, diagnosed with PD (according to the criteria of the Primary Dysmenorrhea Consensus Guideline [34]), and in Cold and Dampness Stagnation pattern (based on a revised Chinese national guideline [30]),moderate to severe primary dysmenorrhea (PD) (≥40 mm on VAS-P) for three consecutive menstrual cycles,duration of PD (self-reported pain) varying from 6 months to 15 years,written informed consent.

#### 2.2.4. Exclusion Criteria

Exclusion criteria are as follows:secondary dysmenorrhea (e.g., endometriosis and fibroids),irregular/infrequent menstrual cycles (i.e., beyond the typical range of 21- to 35-day cycle),complication with severe diseases (e.g., cerebral, liver, kidney, or hematopoietic system diseases), mental defects, or asthma,pregnancy,use of analgesic medication in 24 hours before treatment,having a professional acupuncture background,having potentially poor treatment compliance (e.g., unstable working and living situation or difficulty in following up).

### 2.3. Randomization and Blinding

The central randomization will be performed by the Center for Evidence-Based Chinese Medicine affiliated to Beijing University of Chinese Medicine in China, using complete randomization to generate the random allocation sequence. Once a participant is included, the researcher will contact the randomization center for the group allocation of the participant, and the acupuncturist will be informed by telephone. Participants will be allocated at a 1 : 1 ratio (Figure 1).

The participants will be informed that they will have a 50% chance of being allocated in either of the two acupuncture groups, and both groups will be potentially effective; hence, participants will be blinded to the group allocation. The patients will also be informed of the possible risks associated with acupuncture (hematoma or fainting). The acupuncturist cannot be blinded due to the specific nature of intervention. Outcome assessors and personnel who will deal with data collection and data analysis will be blinded throughout the entire trial.

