Acupuncture is one of the main treatment modalities of TCM. Several trials [21, 22] have already demonstrated the encouraging results of acupuncture as a nonpharmacological option for the treatment of PD. Two systematic reviews also demonstrated the effect [23] and cost-effectiveness [24] of this therapy. The acupoint SP6 (Sanyinjiao) is found to be one of the most commonly used points encountered when searching ancient Chinese medical classics, Chinese acupuncture textbooks, and clinical trials using acupuncture-related therapies for PD [25, 26]. Previous randomized controlled trials have showed that acupuncture at SP6 (Sanyinjiao) can relieve the pain of PD immediately [27–29] especially for PD patients with Cold and Dampness Stagnation pattern [30], which is the most common pattern in PD patients [31, 32]. Langevin's study [7] also showed that, compared with the nonacupoint control group, the average pullout force in SP6 (Sanyinjiao) was greater, which suggested that SP6 (Sanyinjiao) might be especially sensitive in Deqi.

In this study, we will perform a randomized controlled trial using SP6 to investigate the influences of Deqi on immediate analgesia effects in PD patients with Cold and Dampness Stagnation pattern. The primary objective of this trial is to evaluate the influences of Deqi on acupuncture therapy, in terms of pain reduction (measured on a 0–100 mm visual analogue scale for pain (VAS-P)) achieved before and after intervention (i.e., before and after 30 minutes of treatment). The secondary objectives are as follows: (1) to evaluate the influences of anxiety reduction on a 0–100 mm visual analogue scale for anxiety (VAS-A) and (2) to evaluate the influences of temperature changes at SP6 (Sanyinjiao) and CV4 (Guanyuan) acupoints monitor by a digital infrared thermographic imaging device (only in the Dongzhimen Hospital).

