### 2.2. Settings and Participants

A target sample of 96 participants will be recruited in acupuncture clinic from the following four hospitals: Dongzhimen Hospital Affiliated to Beijing University of Chinese Medicine, Beijing Hospital of Traditional Chinese Medicine affiliated to Capital Medical University, Huguosi Hospital of Traditional Chinese Medicine affiliated to Beijing University of Chinese Medicine, and Hebei Medical University. The trial will be conducted from March 2013 to March 2015.

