#### 2.2.1. Sample Size

This is a study without similar references as we know and 40 patients per group is acceptable for calculating sample size for further studies. Assuming a dropout rate of 20%, we will plan to enroll a total of 96 participants with 48 in each group.

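### Complete randomisation across four hospitals does not guarantee the planned 48 per group or balance within centres, including the one hospital that supplies the temperature data

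*Protocol article*

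**What the plan says.** All references are to the protocol article.

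- Section 2.3 (Randomization and Blinding): "The central randomization will be performed by the Center for Evidence-Based Chinese Medicine", with the list generated "using complete randomization to generate the random allocation sequence". It adds "Participants will be allocated at a 1 : 1 ratio" and says that patients are told "they will have a 50% chance of being allocated in either of the two acupuncture groups". Group assignment reaches the acupuncturist by telephone, and the acupuncturist is not blinded. No block or stratum is mentioned.
- Section 2.2.1 (Sample Size): the plan is "a total of 96 participants with 48 in each group", built from 40 per group and 20% dropout.
- Section 2.2 (Settings and Participants): "A target sample of 96 participants will be recruited in acupuncture clinic from the following four hospitals". No enrolment figure is given for any hospital.
- Section 1 (Introduction): the temperature objective is pursued "only in the Dongzhimen Hospital".
- Section 2.4 (Interventions): the Deqi arm receives 30 seconds of manual needle manipulation; the other arm receives none.
- Section 2.8 (Statistical Analysis): repeated-measures ANOVA for VAS-P, VAS-A and temperature; ANCOVA only for comparing demographic and clinical history variables. No centre term is named.

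**The concern.** The article names its method, and that method carries no restriction on arm sizes, either overall or within a hospital. An exact 48 per group is therefore a result that it sometimes produces, not one that it secures. The two sections do not match as written.

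Within centres the issue is more practical. The active treatment is a hand technique, and Section 2.8 accepts that some patients in the Deqi arm will not experience Deqi. Response could well differ between hospitals or operators. If it does, a chance surplus of one arm at one hospital moves the VAS-P and VAS-A comparisons away from the treatment effect in that particular trial. For temperature, all data come from one hospital, so an uneven split there reduces the precision of that whole secondary objective.

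**Working it through.** **Inputs.** Total 96 and 48 per group (Section 2.2.1); allocation probability 0.5 (Section 2.3); four centres (Section 2.2); one temperature centre (Section 1). Centre sizes are not given, so a range is assumed.

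**The plan's own figure.** 40 × 1.20 = 48 per group, and 2 × 48 = 96. This reproduces the stated enrolment.

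**Arm sizes overall.** Under complete randomisation the size of one arm is X ~ Binomial(96, 0.5).

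- P(48:48) = C(96,48)/2^96 = 0.081
- P(43:53 or worse) = 2·P(X ≤ 43) = 0.358
- P(38:58 or worse) = 2·P(X ≤ 38) = 0.052
- P(smaller arm below 40 before any dropout) = 2·P(X ≤ 39) = 0.082

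**Cost overall.** Relative efficiency against an equal split is 4·n1·n2/N².

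- 43:53: 4 × 43 × 53 / 96² = 9116/9216 = 98.9%
- 38:58: 4 × 38 × 58 / 96² = 8816/9216 = 95.7%

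The article states no power or effect size. As an illustration, take a standardised difference of 0.572 (assumed), which gives 80% power at 48:48 with a two-sided 0.05 test. Power is then 79.6% at 43:53 and 78.2% at 38:58.

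**Balance at one centre.** X ~ Binomial(n, 0.5), with n assumed:

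| Patients at the centre | 2:1 split | P(2:1 or worse) |
|---|---|---|
| 12 | 4:8 | 38.8% |
| 24 | 8:16 | 15.2% |
| 36 | 12:24 | 6.5% |
| 48 | 16:32 | 2.9% |

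If all four centres enrolled 24 (a further assumption), the chance of at least one such split is 1 − (1 − 0.1516)^4 = 48%.

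**Cost at the temperature centre.** At 8:16, 4 × 8 × 16 / 24² = 512/576 = 88.9%.

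**Cost for pain and anxiety.** Suppose one centre of 24 splits 8:16 and the other three are even (36:36 together), so the arms are 44 and 52. That centre makes up 8/44 = 18.2% of one arm and 16/52 = 30.8% of the other. If its mean change differs from the rest by D, the unadjusted group difference shifts by (0.308 − 0.182)·D, about 0.126·D. The documents give no value for D.

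**A list fixed at 48:48 but not stratified.** The number in one arm at a centre of 24 is hypergeometric. P(2:1 or worse) is 9.8%, against 15.2% above. Fixing the totals does not settle the centres.

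**The case against.** Simple randomisation from a central telephone service is valid. It is also the least predictable scheme, which counts for something when the acupuncturist knows the allocation. It meets the 1:1 ratio and the 50% chance in expectation, and 48 per group can be read as a planning number. The wording may even be loose for a list fixed at 48:48. The loss of power is small. The outcomes are before-after changes, so stable differences in pain level between hospitals cancel from the group-by-time contrast, and only differences in response matter. A condensed article may also leave block details and model covariates to the full protocol or analysis plan.

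Most of this stands, and it limits the point. Three stronger readings are tempting but not supported:

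- **That the method cannot deliver 48 per group.** It can; it does not guarantee it.
- **That centre confounds the temperature result.** Temperature is measured at one hospital, so centre is constant there. Confounding by operator would need several acupuncturists at that hospital, which the article does not state. What remains is lost precision.
- **That the analysis certainly omits centre.** The article names no centre term, but an analysis plan that is not shown could add one.

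The objection does not remove the core. The article does not leave the method open: it names an unrestricted one. Even the fixed-list reading leaves balance within centres to chance.

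**Conclusion.** The point holds in a limited form. As described, the randomisation gives the planned 48:48 split with probability 8% and does not control balance within hospitals. Allocation remains unbiased, and the overall cost is minor: under 2 points of power at 38:58 in the illustration, a split reached or exceeded about 5% of the time.

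The real exposure is twofold: chance imbalance by centre in the VAS-P and VAS-A comparisons, which matters only if response differs by centre or operator; and reduced precision for temperature, which is appreciable only if that hospital enrols few patients.

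The overall probabilities rest on reading complete randomisation in its usual sense. The within-centre figures rest on assumed centre sizes. That operators differ between hospitals is inferred from there being four sites. The change is worth making because it is cheap, not because the trial is invalid without it.

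**What to change.** 1. Have the existing central service issue permuted blocks of randomly varying, concealed size, stratified by hospital. A largest block of b holds each centre's difference to at most b/2. With blocks of 4 (illustrative) that is 2 per centre and 4 × 2 = 8 overall, so the smaller arm is at least 44 of 96. With blocks of 4 and 6 it is 3 per centre and 12 overall, so at least 42.
2. Include centre as a factor in the VAS-P and VAS-A outcome models so that it acts on the change. In the repeated-measures ANOVA this means a centre-by-time term. It does not belong in the ANCOVA of baseline variables or in the single-centre temperature model.
3. If complete randomisation is kept, describe 48 per group as the expected size and still adjust for centre. If the list is in fact blocked or fixed at 48:48, correct Section 2.3 to say so.

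Cost: a new list from a service already in place; 3 degrees of freedom for four centres (error degrees of freedom for change fall from 96 − 2 = 94 to 91); and slight predictability at the end of a block, limited by varying and concealing the block sizes.

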### 2.4. Interventions

All participants, when their VAS-P score of menstrual pain is equal to or more than 40 mm on the first day of menstruation, will each receive an acupuncture treatment for 30 minutes at bilateral SP6 acupoints. The SP6 lies on the tibial aspect of the leg, is posterior to the medial border of the tibia, and is 3 B-cun (proportional bone cun) superior to the prominence of the medial malleolus [35].

*(a) Deqi Group*. The treatment will be performed after sterilizing the skin on the areas where the needles will be inserted, with participants lying face up. Using single-use sterile needles (Zhongyan Taihe, Wuxi Jiajian Medical Instrument Co. Ltd., Jiangsu, China) of 0.30 mm calibre and 40 mm length, a needle will be vertically inserted 1 cun in depth and will be manipulated by lifting-thrusting and twirling methods for 30 seconds to achieve Deqi.

*(b) No Deqi Group*. Single-use sterile needles (Zhongyan Taihe, Wuxi Jiajian Medical Instrument Co. Ltd., Jiangsu, China) of 0.18 mm calibre and 13 mm length will be used. The treatment will be performed after sterilizing the skin on the areas where the needles will be inserted, with participants lying face up. A needle will be vertically inserted 0.1 cun in depth. No manipulation will be performed after insertion of needles to avoid Deqi.

### 2.5. Outcome Measures

#### 2.5.1. Primary Outcome Measures

The changes of pain will be measured by visual analogue scale for pain (VAS-P), before and after the treatment. The validity and reliability of the VAS-P scale have been proven [36–38] and it was employed in our previous similar studies [29, 30]. The scale measures a continuous quantitative variable varying from 0 mm (no pain) to 100 mm (worst pain ever).

#### 2.5.2. Secondary Outcome Measures

The changes of the anxiety are measured by visual analogue scale for anxiety (VAS-A), before and after the treatment. This scale has been used in a PD study [39]. The scale measures a continuous quantitative variable varying from 0 mm (no anxiety) to 100 mm (almost death).The changes of temperature at SP6 (Sanyinjiao) and CV4 (Guanyuan) acupoints (located at the lower abdomen, 3 B-cun inferior to the centre of the umbilicus, on the anterior median line [35], e.g., in the skin area corresponding to the uterus) are measured by a digital infrared thermographic imaging device (USA, FLIR Systems Inc., SC640) before and after treatment. It is demonstrated that acupuncture can affect skin temperature at the needling acupoint, and it is feasible to detect the changes of the skin temperature by using a thermographic camera at a certain acupoint during acupuncture treatment [40].Adverse events: the possible side effects and adverse reactions during the treatment will be recorded in the case report form (CRF).

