### 2.6. Data Collection

The data required for evaluating the influences of Deqi on acupuncture therapy will be collected at baseline and the completion of intervention. Data will be obtained via physical measurements. Data collection instruments and the study timeline are summarized in Table 1.

A case report form (CRF) has been designed, to include the variables of interest, which will be completed by the corresponding researcher at each research center. After the trial finished, the information obtained will be input to an electronic database, for subsequent statistical analysis.

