## Figures and Tables

**Figure 1 fig1:**
[figure not shown]
Flow diagram for the study. Work scheme with description of assessment visits and times.

**Table 1 tab1:** Data collection at different assessment points. Example of outcome measurements.

Variable	T0	T1
VAS-P	X	X
VAS-A	X	X
ADCAS		X
Temperature at SP6, CV4	X	X
Side effects and adverse reactions		X
Sociodemographic data	X	

Note: VAS-P: visual analogue scale for pain (0–100); VAS-A: visual analogue scale for anxiety (0–100); ADCAS: Acupuncture Deqi Clinical Assessment Scale; SP6: Sanyinjiao; CV4: Guanyuan; T0: before acupuncture treatment; T1: after acupuncture treatment.

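### Adverse-event recording stops at the end of a single 30-minute session, so harms first noticed after the participant leaves would go uncounted

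*Protocol article*

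**What the plan says.** Three places in the protocol article bear on the adverse-event window.

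- **Section 2.5.2** lists adverse events with the secondary outcomes and limits the record to the session: "the possible side effects and adverse reactions during the treatment will be recorded in the case report form (CRF".
- **Table 1** has two columns, T0 and T1. The row headed "Side effects and adverse reactions" carries a single mark, which with the text belongs to T1. The note defines the last point as "T1: after acupuncture treatment" and gives no clock time.
- **Section 2.6** says that the data for evaluating the influence of Deqi "will be collected at baseline and the completion of intervention", and points to Table 1 for the timeline.

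Section 2.4 makes the treatment a single session: participants "will each receive an acupuncture treatment for 30 minutes at bilateral SP6 acupoints". Section 2.3 says that patients are told of "possible risks associated with acupuncture (hematoma or fainting". No later visit, call or message and no period for spontaneous reports is described.

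**The concern.** The article fixes the window; it is not a detail left open for a fuller document. A site that followed it would stop recording harms at T1, in the same visit as the treatment. A haematoma that became visible later that day, or a faint after the participant had left, would have no place in the schedule.

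The wording is also uneven at the boundary. Section 2.5.2 speaks of the treatment itself, while Table 1 speaks of a point after it. Sites could differ on whether an event at needle withdrawal or on getting up counts.

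The descriptive account of harms is at stake. The two arms receive clearly unequal needling, so readers will compare their adverse events even though no formal test is planned. If few or no events are recorded, the result could be taken to describe acupuncture at this point in general, when it describes only the session.

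**Working it through.** The article states no adverse-event rate and no onset time, so there is no figure of its own to reproduce. The check is a side-by-side reading, followed by an illustration on assumed values.

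**Reading**

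1. Length of treatment: one session of 30 minutes (Section 2.4). The Introduction places the pain measurement "before and after 30 minutes of treatment".
2. Recording window: the treatment in Section 2.5.2; T1 in Table 1. On the wider reading the record includes whatever is present at T1, when pain, anxiety and the Deqi scale are also taken.
3. Anything after T1: nothing scheduled. Section 2.2.4 excludes women who would be hard to follow up, but Table 1 contains no follow-up contact.
4. Named risks: haematoma and fainting (Section 2.3), without timing and without distinction by arm.
5. Needling (Section 2.4): Deqi arm, 0.30 mm needle, 1 cun deep, manipulated for 30 seconds; No Deqi arm, 0.18 mm needle, 0.1 cun deep, no manipulation.

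Items 1 to 3 show that an event first noticed after the participant leaves is not captured. Item 5 makes a larger loss in the Deqi arm plausible, but nothing in the article measures it.

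**Illustration (all rates and late shares are assumptions)**

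Let p_D and p_N be the true event rates and f the share of events first noticed after T1, taken as equal in both arms. With 48 per arm (Section 2.2.1):

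- events missed in an arm = 48 × p × f
- observed risk difference = (p_D − p_N) × (1 − f)

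| p_D v p_N | f | Missed, Deqi | Missed, No Deqi | True difference | Observed difference |
|---|---|---|---|---|---|
| 10% v 2% | 25% | 1.2 | 0.24 | 8 points | 6 points |
| 10% v 2% | 50% | 2.4 | 0.48 | 8 points | 4 points |
| 10% v 2% | 75% | 3.6 | 0.72 | 8 points | 2 points |
| 20% v 5% | 25% | 2.4 | 0.6 | 15 points | 11.25 points |
| 20% v 5% | 50% | 4.8 | 1.2 | 15 points | 7.5 points |
| 20% v 5% | 75% | 7.2 | 1.8 | 15 points | 3.75 points |

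Two features limit what the table shows. The proportion lost equals f by construction, so it is not an estimate of the undercount. And with the same f in both arms the risk ratio does not change (10/2 = 5 before and after the loss); only the counts and the absolute difference shrink. If the true rates were equal, the observed difference would stay at zero.

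For scale, if no event were recorded among 48 patients, the exact one-sided 95% upper bound would be 1 − 0.05^(1/48) = 6.05%. That bound would apply to any arm of 48. It does not measure the defect, and here it would describe only events seen up to T1.

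**The case against.** The other side has a good deal to say.

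- **T1 lies after the session.** A haematoma visible when the needles come out can be recorded there. This stands: a reader might infer that the record closes before the named harms can appear at all, but no section says when the case report form closes, and only the later subset is lost.
- **Section 2.6 concerns the data for evaluating the influence of Deqi.** A reader might take it to bar any later data; it does not say that about safety reports. The point therefore rests on Section 2.5.2 and Table 1.
- **The arm imbalance is an inference.** A reader might infer that nearly all missed events fall in the Deqi arm, or that the trial would wrongly show Deqi needling to be as safe as superficial needling. The article gives no rates by arm and no onset times, does not tie fainting to either technique, and announces no such safety claim.
- **Safety is not among the objectives in the Introduction, and Section 2.8 names no test of adverse events.** This stands, and it limits the consequence to the descriptive harms report.
- **A condensed article may leave safety procedures to the full protocol; Figure 1 is not shown; the trial is said to follow good clinical practice.** This would answer a complaint that a detail is absent. It does not answer one about a window that the article states and that its own timeline table matches.

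Same-visit recording can be defended for a trial of immediate pain relief. It then needs to be described as such.

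**Conclusion.** The point holds as a limited one. The stated window ends at T1, and events first appearing or noticed after the participant leaves would be missed, so harms are likely to be undercounted. This rests on one assumption that the article does not test: that some events of the kinds it names come to light only after the visit. A larger loss in the Deqi arm is plausible from the needling described, but neither its size nor its existence can be shown from the article. The rates and late shares in the illustration carry no evidential weight. Pain, anxiety and temperature results do not change. The change is worth making because it costs little, not because the main conclusions are at risk.

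**What to change.** Reword Section 2.5.2 and add a row and a time point to Table 1, so that the adverse-event window runs from needle insertion, through needle withdrawal and getting up, to a fixed later time, for example the next day. Collect the later part by one standard call or message, with the same question asked in the same way in both arms. Report events up to T1 and after T1 separately by randomised arm, with the number who answered the later contact.

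The cost is about 96 short contacts by existing staff and some non-response. The intervention, the primary outcome and the timing of the pain and anxiety scales stay as they are.

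If no later contact is possible, at least define the window to include needle withdrawal and departure, and state in the report that the harms result covers the session only.
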